# A Case Management Program at Home to Reduce Fall Risk in Older Adults (the MAGIC Study): Protocol for a Single-Blind Randomized Controlled Trial

**DOI:** 10.2196/34796

**Published:** 2022-06-13

**Keywords:** accidental falls, risk management, aged, fall prevention

## Abstract

**Background:**

Individual case management programs may be particularly effective in reducing fall risk as they can better identify barriers and facilitators to health recommendations.

**Objective:**

This paper describes the protocol for a single-blind, parallel-group randomized controlled trial that aims to investigate the effectiveness and cost-effectiveness of a home-based multifactorial program targeting fall risk factors among people aged 60 years and over who have fallen at least twice in the past 12 months (the MAGIC trial).

**Methods:**

Older people with a history of at least 2 falls in the last year will be divided into 2 groups. The intervention group will receive case management at home for reducing the risk of falls, including a multidimensional assessment, explanation of fall risk factors, and elaboration and monitoring of an individualized intervention plan based on the identified fall risk factors, personal preferences, and available resources. The control group will be monitored once a month. Assessments (clinical data, fall risk awareness, physical and mental factors, safety at home, feet and shoes, and risk and rate of falls) will be carried out at baseline, after 16 weeks of the intervention, and at the posttrial 6-week and 1-year follow-up. After 16 weeks of the intervention, satisfaction and adherence to the intervention will also be assessed. Economic health will be evaluated for the period up to the posttrial 1-year follow-up.

**Results:**

Data collection started in April 2021, and we expected to end recruitment in December 2021. This case management program will address multifactorial assessments using validated tools and the implementation of individualized intervention plans focused on reducing fall risk factors.

**Conclusions:**

This trial may provide reliable and valuable information about the effectiveness of case management for increasing fall risk awareness and reducing fall risk in older people.

**Trial Registration:**

Brazilian Clinical Trials Registry (ReBec) RBR-3t85fd; https://ensaiosclinicos.gov.br/rg/RBR-3t85fd

**International Registered Report Identifier (IRRID):**

DERR1-10.2196/34796

## Introduction

One of the challenges of aging is the social and health costs arising from falls—a major cause of disability and death among older adults. The economic impact of falls affects family, community, and society [1]. Between 2011 and 2015, 43,400 fall-related deaths and 240,000 fall-related hospitalizations occurred among older Brazilian people [2,3]. In general, falls result from multiple risk factors. Reducing risk factors for falls through an intervention based on case management may be particularly beneficial for preventing falls in older adults [4].

Case management interventions allow professionals to develop and implement individualized plans for preventing falls and consequences [5,6]. The case manager ensures follow-up of the plans in accordance with the older adult and family, identifies barriers to their implementation, and motivates the older person to adhere to the program [5]. Moreover, in a cross-sectional study, the preference of the older people in relation to different formats of programs for falls was verified. Older people with a greater concern about falls and disposition to participate in some program prefer participating in personalized and home-delivered programs based on their individual characteristics, difficulties, and limitations when compared to programs conducted in groups [7].

A Cochrane systematic review has shown that integrated multifactorial assessments and individualized interventions are effective in reducing the rate of falls [8,9]. Although these studies provide good evidence for fall prevention, there is a lack of trials investigating multifactorial interventions based on individualized fall risk factors, such as case management interventions. In addition, there is a need for studies that assess acceptance and adherence to multifactorial programs for reducing fall risk [8,9], taking into consideration monthly falls monitoring and the presence of managers within the work team.

There is a scarcity of randomized controlled trials involving case management for reducing fall risk. Individual case management programs may be particularly effective in reducing fall risk, as they can better identify barriers and facilitators to health recommendations. This model of care can offer physical, psychological, and social assistance that goes beyond the traditional models of health care for fallers.

Considering the aforementioned discourse, we designed a home-based multifactorial program targeting fall risk factors among people aged 60 years and over who have had a fall at least twice in the past 12 months. The proposed intervention program consists of individualized management of fall risk factors. This study protocol details the MAGIC trial, outlining the design of the study, describing their objectives, methodology, and overall organization of the research to be carried out.

## Methods

### Trial Design and Setting

A parallel-group, single-blind randomized controlled trial with a block randomized design (allocation ratio 1:1) will be carried out. The trial will be performed in São Carlos, Brazil, and surrounding cities, where 16% of the local population is aged 60 years and over (Multimedia Appendix 1).

### Study Population

Participants will be recruited through health and social services, open registration via telephone, and a volunteer database of the research group. The study will be promoted via leaflets, posters, social networks, and local radio and television.

Eligible people will be community older adults aged 60 years and over, be residents of São Carlos and surrounding regions, be noninstitutionalized, and have a history of falls in the last year. Inclusion criteria will be having a history of at least 2 falls in the last year, being willing to participate in the interventions and assessments, being able to walk with or without walking devices, and being available to be contacted by telephone. Exclusion criteria will be having severe and uncorrected visual or auditory disorders that affect communication during assessment and intervention, having active inflammatory and neurological diseases that severely interfere with balance performance (advanced Parkinson disease—stage 5 on the modified Hoehn and Yahr Scale and not being regular users of antiparkinsonian medications, multiple sclerosis, Huntington disease, dementia, uncontrolled vestibulopathy, epilepsy, traumatic brain injury, and severe motor sequelae of stroke), or participating in regular and systematic physical activity for a total duration of ≥150 minutes per week.

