### Randomization and Blinding

A randomization sequence will be created by an external researcher with Random Allocation software (Windows Inc) with a 1:1 allocation using random block sizes. The allocation sequence will be concealed from the external researcher enrolling participants in sequentially numbered, opaque, sealed, and stapled envelopes. Corresponding envelopes will be opened after assessment at baseline by another independent researcher, who will be responsible for advising participants of their allocation by telephone.

Assessors will be blinded to randomization until the end of the study. Owing to the nature of the trial, the researchers responsible for the intervention and the volunteers will not be blinded to randomization.

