### Intervention

The intervention protocol follows all protective measures recommended in response to the COVID-19 pandemic. The intervention group (IG) will receive a remote case management intervention at home over 16 weeks, once a week by video or a telephone call. Volunteers who have regular access to the internet and a smartphone or computer made weekly calls through video, while those with limited access were contacted by telephone. The control group (CG) will be followed by monthly telephone calls. The intervention will be carried out by 2 trained researchers, scheduled to start in April 2021.

Case managers are responsible for monitoring the volunteers and their families among the intervention proposals to reduce each of the modifiable fall risk factors in the initial assessment. These managers are trained gerontologists who, in addition to having pre-established proposals, hold discussions fortnightly to discuss cases with the entire intervention team, ensuring the best guidelines for volunteers and the alignment of manager´s actions. According to the Brazilian Society of Geriatrics and Gerontology, gerontologists have training in different areas of knowledge (psychology, social work, nutrition, occupational therapy, law, etc), so they are able to plan, coordinate, and evaluate health actions related to older people; in addition, they can deliver biopsychosocial care.

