#### Secondary Outcome Measures

Secondary outcomes are falls, physical function (muscle strength of lower limbs, balance, and mobility), mental functions (cognition, depressive symptoms, and fear of falling), fall risk, safety at home, feet and footwear, satisfaction with and adherence to the intervention, and health care costs.

Prospective falls will be collected from baseline to 1-year follow-up using falls calendars and monthly telephone calls. Muscular strength of hip, knee, and ankle joints will be evaluated using the Lafayette dynamometer. In addition, muscle strength, mobility, and balance will be assessed with the Brazilian version of the Short Physical Performance Battery (SPPB). The SPPB consists of 3 tests: Balance Test, Gait Speed Test, and Chair Stand Test [14]. The scores range from 0 to 4, and the total ranges from 0 to 12 points, with higher scores indicating better lower limb function [14]. Balance will also be assessed with the MiniBest test, which has a total score of 28 points, and higher scores indicate better balance [15].

Cognition will be assessed with Addenbrooke’s Cognitive Examination-Revised screening battery, which has a maximum score of 100 points, with a score of ≤78 points indicating cognitive impairment [16]. Digit Span Forward will be used to assess attention and immediate memory deficits (indicated by scores less than 6 points) and Digit Span Backward for measuring attention and working memory deficits (indicated by scores less than 4 points) [17]. To assess depressive symptoms, the Geriatric Depression Scale will be used. Higher scores on this 15-point scale indicate a greater risk of depressive symptoms. The Falls Efficacy Scale-International will be used to assess fear of falling [18]. A total score of ≥23 points is associated with occasional falls, and a score of >31 is associated with recurrent falls [18].

Fall risk will be assessed with the Falls Risk Assessment Tool. The score varies from 0 to 5 points, with a score of 3 or more points indicating a high risk of falls [19]. Regarding home safety, the Home Falls and Accidents Screening Tool will be used. The maximum score is 25 points, and higher scores are indicative of a greater risk of falls and home accidents [20].

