## Discussion

The MAGIC trial aims to provide rigorous direct evidence about the effectiveness and cost-effectiveness of a home-based multifactorial program targeting fall risk factors among people aged 60 years and over who have fallen at least twice in the past 12 months. We hypothesize that the IG presents better awareness of fall risk and positive behavior change in reducing fall risk factors identified by case management, thus decreasing new episodes of falls with an increasing volume of physical activity after the 16-week intervention compared to the CG; in addition, we expect that community older people in the IG will continue to show the positive results obtained after the 6-week follow-up compared to the CG.

The strengths of this MAGIC study are the follow-up of individualized case management that offers greater attention to the older people in the home environment and includes the family or caregiver in the action plan for behavior change in order to reduce the identified risk factors for falls. In addition, the program offers monitoring of the older people by a physical therapist to implement a protocol for safe physical activities at home.

The researchers may encounter some limitations during this randomized controlled trial, including difficulties in recruitment, restrictions on home visits owing to the COVID-19 pandemic, and poor compliance with the recommendations proposed by the case managers. If needed, potential solutions will be the use of remote assessments by video and telephone calls and the inclusion of additional recruitment sites.

The findings of this study may provide reliable and valuable information about the effectiveness of case management for increasing fall risk awareness and reducing fall risk in older people. This study protocol detailed the design and methodology of the research to support the transparency of results. This may also assist the design of future studies.

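### Eligibility and individual allocation let two residents of one home enter opposite arms of a family-inclusive intervention, which may dilute the awareness and home-safety contrasts

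*Protocol article*

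**What the plan says.** All references are to the protocol article.

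- **Study Population.** Eligibility is personal: "Eligible people will be community older adults aged 60 years and over, be residents of São Carlos and surrounding regions, be noninstitutionalized". "Inclusion criteria will be having a history of at least 2 falls in the last year", alongside willingness, walking ability and telephone contact. The exclusions end with "or participating in regular and systematic physical activity for a total duration of ≥150 minutes per week". None concerns a household member who is already enrolled. Recruitment routes include open telephone registration, leaflets, radio and television.
- **Randomization and Blinding.** The sequence is made "with a 1:1 allocation using random block sizes", in sequentially numbered envelopes. "Corresponding envelopes will be opened after assessment at baseline by another independent researcher". No household unit is mentioned.
- **Intervention.** "Case managers are responsible for monitoring the volunteers and their families among the intervention proposals". The second session explains the identified risk factors to the participant and the caregiver. The caregiver then helps to develop and carry out the plan. Exercise material comes as videos, guidelines or booklets.
- **Discussion.** It is named as a strength that the program "includes the family or caregiver in the action plan for behavior change in order to reduce the identified risk factors for falls".
- **Outcomes.** The primary outcome is the Falls Risk Awareness Questionnaire (0 to 32), where a higher score means more knowledge of risk factors. Among the secondary outcomes, "Regarding home safety, the Home Falls and Accidents Screening Tool will be used".
- **Results.** At submission, 52 volunteers had been recruited. The target under Power and Sample Size is 60.

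**The concern.** The unit of allocation is the individual, but parts of the intervention reach other people in the home. If two residents both qualify, the stated rules let one enter each arm. When the control resident is also the other's caregiver, the protocol itself directs that the control be taught the risk factors on which the primary score tests knowledge. Even when not the caregiver, a co-resident may hear the weekly calls or see the materials.

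On home safety, the two residents would be scored on the same dwelling, so a split pair can show little contrast on whatever items describe the building.

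At stake is a modest bias towards no difference in a small trial, where a handful of exposed controls is a visible fraction of an arm of 30.

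**Working it through.** **1. The plan's own figure.** Power and Sample Size gives type I error 5%, power 80%, effect size f = 0.20 and two groups, with a result of 42. The number of measurements is not stated there. Outcome Measures (Overview) gives three for the primary outcome: baseline, 16 weeks, and 6 weeks post trial. For the group-by-time interaction:

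- λ = f² × N × m / (1 − ρ) = 0.04 × 42 × 3 / 0.5 = 10.08
- df = (2 − 1)(3 − 1) = 2 and (42 − 2)(3 − 1) = 80
- power = 0.803

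So 42 reproduces if ρ = 0.5 and sphericity are assumed; neither is stated. The household question does not make 42 wrong. The target of 60 less 20% dropout leaves 48 completers, with power 0.857 on the same assumptions.

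**2. How often a pair would be split.** With 30 of 60 in each arm, a given same-home pair is split with probability 30/59 = 0.51. Two residents who fall in the same block of size b are split with probability (b/2)/(b − 1), which also exceeds one half. One enrolled pair thus gives about half a split pair. At 30/59, 1 to 3 split pairs correspond to about 2 to 6 enrolled pairs, or 4 to 12 people (7 to 20% of 60).

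**3. Dilution.** With S split pairs and a fraction t of the effect passing to the exposed control, the control mean moves by (S/30) × t of the effect. The contrast is multiplied by 1 − S × t/30, and f with it. S and t are assumptions; the article gives neither.

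| S | t | Dilution | f | Power, N = 42 | Power, 48 completers |
|---|---|---|---|---|---|
| 0 | – | 0% | 0.200 | 0.80 | 0.86 |
| 1 | 0.5 | 1.7% | 0.197 | 0.79 | 0.85 |
| 1 | 1 | 3.3% | 0.193 | 0.77 | 0.83 |
| 2 | 0.5 | 3.3% | 0.193 | 0.77 | 0.83 |
| 2 | 1 | 6.7% | 0.187 | 0.74 | 0.80 |
| 3 | 0.5 | 5.0% | 0.190 | 0.76 | 0.82 |
| 3 | 1 | 10.0% | 0.180 | 0.71 | 0.77 |

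The margin in the target of 60 absorbs about two fully exposed controls.

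**4. Standard error.** Let D be the number of pairs that land in the same arm and r the within-home correlation. With n per arm, the variance of the difference in means is (2σ²/n) × [1 + (D − S) × r/n]. Split pairs lower it and same-arm pairs raise it. With 30/59 expected split and 29/59 together, the two nearly cancel.

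**The case against.** The strongest reply is that this is silence in a condensed article. Nothing says that co-residents were or will be enrolled, and a full protocol may hold a household rule. That possibility stands. However, the article reports its eligibility criteria and its allocation method at length. The point concerns how those stated rules fit a stated family-inclusive intervention, not a detail left out.

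Frequency also counts against the point. Both residents must each have at least two falls in a year, do less than 150 minutes of exercise a week, pass the neurological exclusions and volunteer. Several pairs among 60 would be unusual. This stands and limits the size.

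Stronger readings that a reader might infer, and why the article does not support them:

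- *The co-resident control receives the intervention.* It is delivered by weekly remote calls to the volunteer. The plan rests on that person's own assessment and preferences, and exercise requires that person's medical certificate. A co-resident need not be the caregiver. Exposure is possible; full receipt is not.
- *Split households threaten assessor blinding.* Assessments are done in participants' homes, so materials could be seen in any intervention home. A household rule would leave nearly all of that in place.
- *Shared homes make the standard error too small.* For split pairs the direction is the opposite, as shown in the working.
- *The home-safety contrast is zero by construction.* The article does not list the tool's items, so only a substantial overlap can be inferred. The outcome is also secondary.

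Finally, with 52 of 60 recruited, an eligibility line reaches at most 8 more people. That is right, and it moves most of the remaining value to the address check.

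**Conclusion.** The point holds in a limited form. The stated criteria and individual allocation permit opposite-arm co-residents, and the stated intervention can carry primary-outcome content to the control member of such a pair. The bias is mainly towards no difference, so it would not manufacture a benefit.

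Its size rests on assumption. For 1 to 3 split pairs the dilution is about 3 to 10% with full transfer and about 2 to 5% with half transfer; it is zero with no pairs. At 48 completers, power stays at or above 0.80 in every case shown except three fully exposed controls (0.77), given ρ = 0.5 and sphericity. The stated sample size is unaffected. This is a low-cost improvement, not a flaw that undermines the trial.

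**What to change.** **Remaining enrolments, if any.** Add to Study Population that only one person per household is randomised. Check the address before the envelope is opened. Baseline assessment already precedes that step and already records whether the person lives alone.

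**The 52 already recruited.** Check addresses and report how many households contribute more than one participant, and how many of these are split between arms. If there are any, prespecify, before outcomes are compared by arm, a sensitivity analysis that keeps only the first-randomised member of each household. The intention-to-treat analysis stays primary and unchanged. This analysis restores one person per home, but a first-randomised control who lives with a later intervention participant stays in it, so the count of split homes should be read beside it.

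**Cost.** One eligibility line, an address check and, only if needed, one further analysis. The 42 and the 60 do not change. The downside is that a few otherwise eligible co-residents are not randomised.

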### Outcome Measures

#### Overview

Assessments will be conducted at participants’ homes at baseline, after 16 weeks of the intervention, and at 6 weeks and 1 year post trial completion. The volunteers will be instructed to wear comfortable clothing, closed shoes, not to perform vigorous exercises the day before the assessment, and to wear hearing or visual aids if needed.

Baseline assessments include sociodemographic measures (age, sex, race, marital status, years of schooling, living alone, and income) and general health (BMI; medication use; morbidities; foot problems including dryness of skin, calluses, fissures, open ulcers, and deformities; history of falls, hospitalizations, level of physical activity measured with the Modified Baecke Questionnaire for the Elderly; general health assessed with the Self-Rated Health questionnaire; functional activities evaluated with the Lawton-Brody Scale; and risk of fracture measured with the Fracture Risk Assessment Tool—FRAX).

Primary and secondary outcomes will be reassessed after 16 weeks of the intervention and at the posttrial 6-week follow-up. In addition, after 16 weeks of the intervention, satisfaction and adherence to the intervention will also be assessed among the IG participants. Prospective falls will be collected from baseline to 1-year follow-up. The economic health assessment will be carried out for the period up to the posttrial 1-year follow-up.

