### Power and Sample Size

For the primary outcome (fall risk awareness), the sample size was calculated using the G*Power 3.1 software, based on type of study design (2-way ANOVA), type I error of 5%, statistical power of 80%, moderate effect size (0.20), and number of groups (n=2). This revealed that a total sample size of 42 is required. Allowing for 20% dropout, we will recruit a sample size of 60 people.

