### Statistical Analysis

For statistical analysis, a significance level of 5% will be adopted, and SPSS (version 22.0; IBM Corp) will be used. The analysis will be performed by intention to treat. The Kolmogorov-Smirnov normality test will be applied for all continuous variables to verify data distribution. To compare groups with regard to clinical and sociodemographic characteristics, the chi-square association test and the independent samples *t* test will be used. To test the interaction between groups and assessments, a 2-way, repeated measures ANOVA will be used. If an interaction is identified, simple main effects analyses will be performed, with adjustment for multiple comparisons (Bonferroni correction). To verify which factors influence adherence to the intervention (frequency of ≥70%), a univariate logistic regression analysis will be used. To check which factors influence satisfaction with the intervention, a simple linear regression analysis will be applied.

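### The only stated between-arm analysis names no adjustment for prior-year falls; adding it costs almost nothing and may gain some precision on the fall outcome

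*Protocol article*

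**What the plan says.** All references are to the protocol article.

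- **Study Population** sets a floor on prior falls and no ceiling: "Inclusion criteria will be having a history of at least 2 falls in the last year".
- **Outcome Measures, Overview** lists fall history among the baseline general-health items: "history of falls, hospitalizations, level of physical activity measured with the Modified Baecke Questionnaire for the Elderly". It does not say whether the number of falls is recorded.
- **Randomization and Blinding** describes concealed 1:1 allocation in random blocks. It states no stratification factor.
- **Secondary Outcome Measures** names falls first and collects them prospectively from baseline to the 1-year follow-up. The **Discussion** includes fewer new falls in the hypothesis.
- **Statistical Analysis** gives one method for comparing outcomes between arms: "To test the interaction between groups and assessments, a 2-way, repeated measures ANOVA will be used". No covariate is named. Baseline characteristics are compared by chi-square and t tests, and nothing is said about acting on those results.

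**The concern.** Among people who have all fallen at least twice, the prior-year count can still run from 2 to very many, and it is a natural predictor of later falls. Neither the stated allocation nor the stated analysis uses it.

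Two things are at stake. The first is precision: if the prior count predicts later falls, leaving it out gives a wider interval for the fall rate ratio than the same participants could support. The second is prespecification. Baseline significance tests are planned and no rule on adjustment is given, so a decision to adjust could follow those tests or the fall results themselves. With about 24 to 30 people per arm, some chance imbalance in very frequent fallers is plausible, so the question may well arise.

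**Working it through.** **The plan's own figure.** The sample size rests on fall risk awareness, not on falls. Inputs from Power and Sample Size are alpha 0.05, power 0.80, f = 0.20 and two groups. Three assessments follow from Overview (baseline, then "Primary and secondary outcomes will be reassessed after 16 weeks of the intervention and at the posttrial 6-week follow-up"). Assuming within-person correlation 0.5 and sphericity, for the group-by-time interaction:

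- λ = N f² m / (1 − ρ) = 42 × 0.04 × 3 / 0.5 = 10.08, with df = 2 and (42 − 2) × 2 = 80.
- Power is 0.803, so the stated 42 reproduces.
- 42 / 0.80 = 52.5, so 53 would cover 20% dropout. The 60 recruited leave 60 × 0.80 = 48 completers, about 24 per arm.

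**Assumed inputs for falls.** The article gives none of these:

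- Individual rates are gamma distributed, with a population mean of 1 or 2 falls a year.
- Dispersion is the variance of a person's rate relative to the mean.
- The prior-year count is Poisson, kept only if it is 2 or more.
- The follow-up count is Poisson on a rate correlated with the prior-year rate. Correlation 1 means the same underlying rate before and after baseline.
- There is no treatment effect.

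**Small-sample simulation.** 24 per arm, 16 + 52 = 68 weeks of follow-up, dispersion 0.5 to 1.5, negative binomial fits, 400 or 600 trials per scenario where the number is recorded. The measure is variance of the log rate ratio adjusted for log(prior count), divided by the unadjusted variance. Ranges are over scenarios and repeat runs.

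| Correlation of rates | Variance ratio | Largest cut |
|---|---|---|
| 1.0 | 0.57 to 0.98 | 43% |
| 0.8 | 0.81 to 1.03 | 19% |
| 0.6 | 0.95 to 1.01 | 5% |
| 0.5 | 0.95 to 1.05 | 5% |

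Ratios above 1 are compatible with simulation error plus the degree of freedom spent.

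**One scenario followed through** (rate 2, dispersion 1). At correlation 1 the ratio is 0.63 to 0.65. The 95% interval narrows from ×/÷1.59 to ×/÷1.46, and (ln 1.59 / ln 1.46)² = (0.464 / 0.378)² ≈ 1.5, equivalent to about 50% more participants. At correlation 0.8 the ratio is 0.87 (1 / 0.87 = 1.15, about 15% more). At 0.6 it is 0.95 (1 / 0.95 = 1.05, about 5% more).

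**Large-sample check.** Poisson regression with robust standard errors, one year of follow-up, scaled to 48 completers. The last column is the SD of the shift in log rate ratio caused by chance imbalance in the prior count.

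| Dispersion, rate | Correlation | Variance ratio | SE, unadjusted → adjusted | Shift SD |
|---|---|---|---|---|
| 1, 1 | 0.3 | 0.992 | 0.365 → 0.364 | 0.030 |
| 1, 1 | 0.6 | 0.962 | 0.323 → 0.317 | 0.056 |
| 1, 1 | 0.9 | 0.899 | 0.284 → 0.269 | 0.077 |
| 1, 2 | 0.3 | 0.985 | 0.325 → 0.323 | 0.037 |
| 1, 2 | 0.6 | 0.923 | 0.293 → 0.282 | 0.073 |
| 1, 2 | 0.9 | 0.771 | 0.259 → 0.227 | 0.107 |
| 2, 1 | 0.3 | 0.989 | 0.428 → 0.425 | 0.041 |
| 2, 1 | 0.6 | 0.937 | 0.360 → 0.348 | 0.078 |
| 2, 1 | 0.9 | 0.792 | 0.294 → 0.261 | 0.110 |

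The cut is 1% to 23%. The typical imbalance shift is between 0.030 / 0.365 = 0.08 and 0.107 / 0.259 = 0.41 of an unadjusted standard error. Power is Φ(|ln RR| / SE − 1.96). At a rate ratio of 0.7, the best row moves from Φ(0.357 / 0.259 − 1.96) = 0.28 to Φ(0.357 / 0.227 − 1.96) = 0.35. Across all rows, adjusted power is 0.13 to 0.35.

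**The case against.** **The article states no analysis specific to falls, so an unadjusted one is an inference.** This stands in part. It would be too strong to say the plan ignores prior falls: the ANOVA sentence is generic, and a fuller document might name covariates. But Statistical Analysis is specific about tests, post hoc correction and regressions for adherence and satisfaction, and the one between-arm model it states has two factors and no covariate. The point is an inexpensive improvement to that text, not an error in it.

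**Prior-year falls might enter the ANOVA as the baseline assessment.** Possible, and the text does not settle it. Falls as an outcome are collected from baseline onward, so that reading is not established. Under it, the prior count would enter as an outcome value rather than as a covariate.

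**The count may not be held.** This stands. The baseline item is fall history, and eligibility needs only a threshold of two. The number is implied, not stated.

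**The gain may be small.** This stands. Truncation at two or more falls removes part of the covariate's information, and with moderate stability nothing measurable is gained.

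**Imbalance is not bias.** This also stands. A reader might infer that a few frequent fallers landing in one arm would invalidate the fall result. Under concealed randomization the unadjusted comparison remains valid, and its standard error already allows for such imbalance.

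**Conclusion.** The point holds as a low-cost improvement. As stated, neither allocation nor analysis uses prior-year falls in the between-arm comparison, although fall history is taken at baseline.

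The expected gain is uncertain. With about 24 per arm, rate 1 to 2 a year and dispersion 0.5 to 1.5, it is roughly nil at correlation 0.5, at most about 15 to 20% of the variance at 0.8, and about 40% only under full stability. A reader might infer that leaving out the covariate costs the equivalent of half as many participants again. That figure needs an identical underlying rate before and after baseline in one of the more favourable scenarios, and nothing in the article supports treating it as typical.

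Adjustment would not make the trial well powered for falls at a rate ratio of 0.7. Falls are secondary, and the stated 42 and 60 are unaffected. The firmer benefit is that the choice to adjust is fixed in advance.

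**What to change.** Add to Statistical Analysis, in substance: *Every between-arm comparison of falls adjusts for the number of falls in the 12 months before baseline, entered as log(count), whatever the baseline tests show; the unadjusted estimate is reported beside it.* The log is always defined, because every eligible participant has a count of at least 2. The sentence can sit in whichever fall model is named, provided that model takes covariates.

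Confirm that the baseline fall-history item records the number of falls. The article reports 52 people already recruited, so check their forms as well; a number that was never recorded could be recovered only by later recall.

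Cost: one sentence and one degree of freedom. If the number is on file, no new data are needed. Fix the rule before fall data are examined by arm.
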